## Abstract

Ticagrelor is a direct acting on the P2Y12 receptor blocker, which provides faster and greater platelet inhibition than clopidogrel. However, several studies suggested that in ST-segment elevation myocardial infarction patients undergoing percutaneous coronary intervention (PCI), ticagrelor exhibits initial delay in the onset of antiplatelet action. Unlike ST-segment elevation myocardial infarction, in non-ST-segment elevation acute coronary syndrome (NSTE-ACS), management pathways are highly variable, and some patients may require surgery. Effect of higher loading dose (LD) of ticagrelor in patients with NSTE-ACS in providing faster and stronger inhibition of platelet aggregation is unknown and needs to be explored further.

The AntiPlatelet Effect of different Loading dOse of Ticagrelor trial is an interventional, randomized, open-label, multicenter, phase IV trial designed to evaluate whether a high LD (360 mg) of ticagrelor compared with the conventional LD (180 mg) will result in a higher inhibition of platelet aggregation without increasing bleeding events in NSTE-ACS participants undergoing PCI.

A total of 250 NSTE-ACS participants will be randomized to receive a ticagrelor LD (360 or 180 mg), followed by a maintenance dose of 90 mg twice a day (bid) starting 12 hours after the LD. The primary endpoint is platelet reactivity index measured by vasodilator-stimulated phosphoprotein phosphorylation 2 hours after the LD, and the secondary endpoints include occurrence of periprocedural myocardial infarction and bleeding events.

The AntiPlatelet Effect of different Loading dOse of Ticagrelor trial will provide important information on the risks and benefits of a high LD (360 mg) of ticagrelor in achieving a faster and stronger platelet inhibition compared with the conventional LD (180 mg) in NSTE-ACS patients undergoing PCI.

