## METHODS

### Study Objectives

The APELOT trial (NCT01962428) will assess the hypothesis that a high LD (360 mg) of ticagrelor will result in greater platelet inhibition compared with the conventional LD of ticagrelor (180 mg) in NSTE-ACS patients undergoing PCI.

The primary endpoint is platelet reactivity index (PRI) measured by vasodilator-stimulated phosphoprotein phosphorylation (VASP-P) (2 h after the LD). The secondary endpoints include: the PRI measured by VASP-P at 0.5, 1, 8, and 24 hours after the LD; occurrence of periprocedural myocardial infarction (PMI); and occurrence of in-hospital and 1-month bleeding event (Bleeding Academic Research Consortium score types 1–5). The safety objective is to assess the safety and tolerability of different LDs of ticagrelor in Chinese patients with NSTE-ACS by evaluating adverse events. Additional exploratory objectives will compare the occurrence of in-hospital and 1-month death, myocardial infarction, stroke, and target vessel or target lesion revascularization with a double LD (360 mg) of ticagrelor.

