### Study Design and Study Drug Administration

The APELOT trial is an interventional, randomized, open-label, multicenter, phase IV clinical trial that will recruit participants from 8 centers in Beijing, China. All centers would have highly trained experienced personnel. A total of 250 participants with NSTE-ACS who meet the entry criteria will be enrolled and randomized. The flow chart of the study design is shown in Figure 1.

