### Data analyses

#### Sample Size Justification

On the basis of onset/offset and respond studies, we expected that a double LD (360 mg) of ticagrelor will result in an absolute increase in IPA of 27% compared with the conventional LD (180 mg) of ticagrelor. With the assumption of a difference of 5.7 and a standard deviation (SD) of 16.344 PRI, and the covariate (baseline PRI) with an *R*^2^ value of 0.2, a total of 114 participants will be required in each arm to achieve a 90% power and a 2-sided alpha of 0.05. Considering a dropout rate of 10%, at least 250 participants would be required to complete the study to reach statistical significance.

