### Implications

The APELOT trial will evaluate whether a high LD (360 mg) of ticagrelor will result in greater platelet inhibition compared with the conventional LD (180 mg) of ticagrelor in NSTE-ACS patients undergoing PCI. Despite optimal evidence-based treatment, NSTE-ACS participants were reported to have worse mid-term and long-term prognoses than STEMI participants with more frequent recurrent ischemic events and a 2-fold higher death rate at 2 years. Effective treatment strategy for such participants is yet to be established. If the APELOT trial confirms a higher LD of ticagrelor will have higher IPA and faster onset before PCI, it would help clinicians to choose the optimal antiplatelet therapy in patients with NSTE-ACS undergoing PCI. In addition, it would facilitate PCI procedures and improve clinical outcomes in patients with NSTE-ACS. The results of this study may have a direct impact on the future treatment for patients with NSTE-ACS, and may pave the way for future treatment recommendations.

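### The Abstract sets a no-increase-in-bleeding aim that the hypotheses and sample size do not carry, and that 250 participants cannot establish

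*Protocol article*

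**What the plan says.** The Abstract gives the trial a two-part purpose: to find out whether 360 mg, against 180 mg, "will result in a higher inhibition of platelet aggregation without increasing bleeding events in NSTE-ACS participants undergoing PCI".

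The body is narrower. Under Study Objectives the trial "will assess the hypothesis that a high LD (360 mg) of ticagrelor will result in greater platelet inhibition compared with the conventional LD", with no bleeding element, and the Introduction ends on the same hypothesis. Bleeding is one of the secondary endpoints: "occurrence of in-hospital and 1-month bleeding event (Bleeding Academic Research Consortium score types 1–5". A separate safety objective covers safety and tolerability through adverse events.

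The size follows the body. Under Study Design, "A total of 250 participants with NSTE-ACS who meet the entry criteria will be enrolled and randomized". The Sample Size Justification starts "With the assumption of a difference of 5.7 and a standard deviation (SD) of 16.344 PRI" and concludes that "a total of 114 participants will be required in each arm to achieve a 90% power and a 2-sided alpha of 0.05". It contains no bleeding rate, no margin for an acceptable increase and no power for bleeding.

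Statistical and Analytical Plans gives a 0.05 significance level in a sentence worded for least-squares mean differences. It also plans Cox hazard ratios with 95% confidence intervals, without naming the outcome.

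**The concern.** Higher inhibition is a superiority question. No increase in bleeding is a different kind of claim: it is supported only when the data exclude an increase large enough to matter. A trial sized on a pharmacodynamic measure may estimate bleeding too imprecisely for that.

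What is at stake is the conclusion. If PRI is lower with 360 mg and the bleeding comparison is not significant, the Abstract's aim would appear to have been met in full, even though the data could be compatible with a material excess of bleeding. The Introduction itself cites a meta-analysis that found more major bleeding with thienopyridine pretreatment in this population, so the question is not idle.

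**Working it through.** **1. The plan's own figure.** There is no bleeding calculation to reproduce. The 114 per arm concerns PRI. With SD 16.344 × √(1 − 0.2) = 14.619, the usual formula gives 2 × (1.960 + 1.282)² × 14.619² / 5.7² = 138.2, so 139 per arm at two-sided 0.05 and 90% power. The gap from 114 is a separate matter and is not used below.

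**2. Inputs.** From the article: 250 participants and equal arms, so 125 per arm; two-sided 0.05. Assumed, because the article gives none: bleeding rate p of 3%, 5%, 10%, 15% or 20% in the 180 mg arm.

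**3. Methods.**
- Power: exact binomial enumeration of the pooled two-proportion test, two-sided 0.05, 125 per arm.
- 95% confidence interval half-width with equal rates: 1.96 × √(2p(1 − p)/125). At p = 10%: 1.96 × √(0.18/125) = 1.96 × 0.0379 = 7.4 points.
- Smallest increase that can be excluded with 80% power when the true rates are equal (one-sided 0.025): (1.960 + 0.842) × √(2p(1 − p)/125). At p = 10%: 2.802 × 0.0379 = 10.6 points.

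**4. Results, 125 per arm.**

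| Assumed rate, 180 mg | Power, 1.5-fold rise | Power, doubling | 95% CI half-width (points) | Smallest increase excludable (points) |
|---|---|---|---|---|
| 3% | 8% | 19% | 4.2 | 6.0 |
| 5% | 12% | 32% | 5.4 | 7.7 |
| 10% | 22% | 60% | 7.4 | 10.6 |
| 15% | 33% | 82% | 8.9 | 12.7 |
| 20% | 45% | 94% | 9.9 | 14.2 |

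**5. Reading the table.** Suppose the two arms bleed at exactly the same observed rate. At 5%, the upper limit of the difference is 5.4 points, which corresponds to 10.4% in the 360 mg arm, about twice the control rate. At 10% it corresponds to 17.4%, about 1.7 times. At 20% it corresponds to 29.9%, about 1.5 times.

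**6. Sensitivity.**
- With 10% dropout (250 × 0.9 = 225, about 112 per arm) the figures worsen slightly; power for 5% against 10% falls from 32% to about 30%.
- At an assumed control rate of 30%, power is 69% for a 1.5-fold rise and above 99% for a doubling, but the half-width is 11.4 points.
- At 2%, 125 per arm can exclude a 5-point rise with 80% power, but that accepts 7% against 2%, or 3.5 times the control rate.

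**The case against.** The strongest reply is that this is one clause in an abstract. The body already limits the hypothesis to platelet inhibition and places "occurrence of in-hospital and 1-month bleeding event" among the secondary endpoints. Sizing a pharmacodynamic trial on its primary endpoint is ordinary practice. A margin could be set in a full protocol or analysis plan that is not shown.

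Most of this stands. Sizing on PRI is no error, and the absence of a margin from a condensed article is not the point. But the Abstract states the no-increase limb as part of what the trial is designed to evaluate, and the body does not match it. A later document could supply a margin, but not the precision that 250 participants lack.

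Some stronger readings are tempting, and the article does not support them:
- A reader might infer that P<0.05 is the trial's rule for bleeding. That sentence concerns least-squares mean differences, and hazard ratios with confidence intervals are also planned. The article simply fixes no rule for bleeding.
- A reader might infer that a non-significant result will be reported as safe. No section says so; the risk lies in how the Abstract's aim could be read.
- A reader might infer that any important rise would probably be missed. That is too broad: a doubling would more likely than not be detected at control rates of 10% or more (60%, 82% and 94% at 10%, 15% and 20%). BARC types 1–5 include minor bleeding, so such rates cannot be ruled out.
- The Implications sentence that "it would facilitate PCI procedures and improve clinical outcomes in patients with NSTE-ACS" is optimistic, but it is discussion prose conditional on a positive result. It alters no endpoint or analysis and adds nothing to the bleeding argument.

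**Conclusion.** The point holds as a mismatch between the Abstract's aim and what the trial is set up to test, together with a limit on what it can conclude. At assumed control rates of 3% to 20%, power for a 1.5-fold rise in bleeding runs only from about 8% to 45%, and equal rates would still leave about ±4 to ±10 percentage points of uncertainty. A non-significant bleeding comparison therefore could not establish no increase.

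The size depends on rates that the article does not give. The conclusion is firm for moderate increases across that range. It does not extend to a doubling when bleeding is common. Nothing here faults the pharmacodynamic hypothesis or the choice to size the trial on PRI.

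**What to change.** 1. Bring the Abstract's aim into line with the body: greater platelet inhibition at 2 hours, with bleeding as a secondary endpoint that is estimated.
2. Report the bleeding comparison as the 360 mg minus 180 mg risk difference, or as the hazard ratio, with its 95% confidence interval.
3. State that the upper confidence limit is the basis for any safety statement, and that P≥0.05 will not be taken as showing no increase.

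This needs changes of wording in the aim, analysis and conclusion only, with no change to sample size or conduct. The cost is a more modest safety claim. Keeping the no-increase aim would instead need a justified margin and a trial sized for it. For example, excluding a 5-point rise with 80% power at one-sided 0.025 would take about 299 per arm at an assumed 5% rate and 566 per arm at 10%.

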## INTRODUCTION

Rupture or erosion of an atherosclerotic plaque results in platelet activation, which is the key process in the formation of thrombus or embolus.^1^ Most cases of acute coronary syndrome are due to limited blood flow to the coronary muscles because of thrombotic occlusion of the artery. Non-ST elevation acute coronary syndrome (NSTE-ACS) usually occurs because of partial occlusion of a major coronary artery or complete occlusion of a minor coronary artery. The 1-year incidence of NSTE-ACS exceeds 1.5/1000 people, reflecting the substantial global healthcare burden from the disorder. Patients with NSTE-ACS are found to experience frequent recurrent ischemic events and a 2-fold higher death rate at 2 years despite optimal evidence-based therapy.^2–7^ Thrombotic complications after percutaneous coronary intervention (PCI) and recurrence of ischemic events in patients with ACS can be prevented by dual antiplatelet therapy with aspirin and clopidogrel. Early treatment with a P2Y12 receptor antagonist leads to a higher inhibition of platelet aggregation (IPA) in patients with unknown coronary artery anatomy before diagnostic coronary angiography and prevents recurrent atherothrombotic events in patients undergoing PCI. The 2007 European Society of Cardiology (ESC) level I-A recommends pretreatment with a loading dose (LD) of 300 mg of clopidogrel immediately after NSTE-ACS diagnosis, followed by a daily maintenance dose (MD) of 75 mg.^1^ However, in the present study, the LD of ticagrelor was not administered to patients. In the ONSET/OFFSET study, the onset and offset of antiplatelet effect of ticagrelor was statistically superior to high-dose clopidogrel (600 mg) in patients with stable coronary artery disease.^8^

Fast, uniform, and marked P2Y12 inhibition is recommended in patients with ST-segment elevation myocardial infarction (STEMI) undergoing PCI. The anti-ischemic effect of ticagrelor, with no excess bleeding, was superior to clopidogrel in the STEMI cohort in a subgroup analysis of the PLATelet inhibition and patient Outcomes trial. However, optimal IPA was rarely reached before 1 hour in a few studies. This effect may be because of specific conditions and a prethrombotic milieu that may modify the absorption, metabolism, and subsequent pharmacokinetics and pharmacodynamics of antiplatelet agents.^9,10^ More than one-half of the patients (n = 28) in a prospective, single-center, single-blind study had high platelet reactivity (HPR) at 1 hour of 180-mg (LD) ticagrelor treatment, demonstrating a delayed onset of antiplatelet action.^11^ Based on this observation, it is possible for patients with STEMI to theoretically achieve a faster platelet inhibition with a higher LD. In a prospective, 4-center, nonrandomized, controlled study, the authors hypothesized that doubling the standard 180 mg LD of ticagrelor might result in a higher drug concentration earlier, thereby providing a faster onset of antiplatelet activity. However, this hypothesis could not be confirmed, and doubling the LD of ticagrelor did not result in a faster onset of antiplatelet action than the standard dose.^12^

On the contrary, the degree of IPA achieved with a higher LD of ticagrelor in patients with NSTE-ACS remains to be explored. A recent systematic review and meta-analysis demonstrated a significant increase in major bleeding events and no significant reduction in mortality after pretreatment with thienopyridines in patients with NSTE-ACS.^2^

Significant global healthcare burden of NSTE-ACS and nonexistence of a standardized treatment regimen in patients with NSTE-ACS warrant more research in this domain. The AntiPlatelet Effect of different Loading dOse of Ticagrelor (APELOT) study intends to test the hypothesis that a high LD (360 mg) of ticagrelor will result in greater platelet inhibition than the conventional LD (180 mg) of ticagrelor in patients with NSTE-ACS undergoing PCI.

## METHODS

### Study Objectives

The APELOT trial (NCT01962428) will assess the hypothesis that a high LD (360 mg) of ticagrelor will result in greater platelet inhibition compared with the conventional LD of ticagrelor (180 mg) in NSTE-ACS patients undergoing PCI.

The primary endpoint is platelet reactivity index (PRI) measured by vasodilator-stimulated phosphoprotein phosphorylation (VASP-P) (2 h after the LD). The secondary endpoints include: the PRI measured by VASP-P at 0.5, 1, 8, and 24 hours after the LD; occurrence of periprocedural myocardial infarction (PMI); and occurrence of in-hospital and 1-month bleeding event (Bleeding Academic Research Consortium score types 1–5). The safety objective is to assess the safety and tolerability of different LDs of ticagrelor in Chinese patients with NSTE-ACS by evaluating adverse events. Additional exploratory objectives will compare the occurrence of in-hospital and 1-month death, myocardial infarction, stroke, and target vessel or target lesion revascularization with a double LD (360 mg) of ticagrelor.

### Study Design and Study Drug Administration

The APELOT trial is an interventional, randomized, open-label, multicenter, phase IV clinical trial that will recruit participants from 8 centers in Beijing, China. All centers would have highly trained experienced personnel. A total of 250 participants with NSTE-ACS who meet the entry criteria will be enrolled and randomized. The flow chart of the study design is shown in Figure 1.

**FIGURE 1 F1:**
[figure not shown]
Study flow chart.

After providing written informed consent, all participants will be randomized to receive a ticagrelor LD of 360 or 180 mg, and then a ticagrelor MD of 90 mg bid starting 12 hours after the LD. PCI will be performed within 2 to 72 hours after administration of the LD. All participants would receive acetylsalicylic acid 75 to 100 mg daily until they can tolerate. Glycoprotein IIb/IIIa receptor antagonists and low-molecular-weight heparin and other additional medication will be administered as directed by the treating cardiologist. All interventions will be performed via the radial approach with the standard technique within 72 hours after administration of the LD, and drug-eluting stents will be placed according to stenosis of the coronary artery. Blood samples of all participants will be obtained for the following assessments: PRI measured by VASP-P at predose and at 0.5, 1, 8, and 24 hours after the LD; and serum creatine kinase MB, troponin I, myoglobin, and C-reactive protein at predose, before PCI, and at 8 and 24 hours after PCI. ECG will be conducted at predose and at 8 and 24 hours after PCI. Incidences of PMI, in-hospital and 1-month bleeding events, death, myocardial infarction, stroke, and target vessel or target lesion revascularization will be documented. Participants will be followed up at the clinics or telephoned for 1 month.

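### The listed PRI sampling times leave out the 2-hour draw that defines the primary endpoint, so the article contradicts itself and its text must be reconciled

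*Protocol article*

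**What the plan says.** Three statements bear on when PRI is measured.

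- **Primary endpoint.** The Abstract has "The primary endpoint is platelet reactivity index measured by vasodilator-stimulated phosphoprotein phosphorylation 2 hours after the LD". Study Objectives gives the same time: "The primary endpoint is platelet reactivity index (PRI) measured by vasodilator-stimulated phosphoprotein phosphorylation (VASP-P) (2 h after the LD".
- **Secondary PRI endpoints.** Study Objectives lists "the PRI measured by VASP-P at 0.5, 1, 8, and 24 hours after the LD". The 2-hour time is rightly not in this list, because it is the primary.
- **Blood sampling.** The paragraph after Figure 1, under Study Design and Study Drug Administration, introduces the assessments for which blood will be taken from all participants. For PRI it gives "PRI measured by VASP-P at predose and at 0.5, 1, 8, and 24 hours after the LD". The same sentence then schedules other bloods: "serum creatine kinase MB, troponin I, myoglobin, and C-reactive protein at predose, before PCI, and at 8 and 24 hours after PCI".

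That paragraph also sets the procedure window: "PCI will be performed within 2 to 72 hours after administration of the LD".

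**The concern.** The sampling sentence does not defer its times to another document. It gives a definite list, and the one PRI time missing from it is the one on which the trial's main conclusion rests. The list matches the secondary endpoints with predose added, which suggests that it was copied from the secondary list without adding the primary time.

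What is at stake is collection of the primary outcome. Sample Size Justification is built on PRI ("With the assumption of a difference of 5.7 and a standard deviation (SD) of 16.344 PRI") with baseline PRI as the covariate. Under the list as written the covariate would be measured, at predose, but the 2-hour outcome would not. A timed sample that is not drawn cannot be taken afterwards.

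**Working it through.** The plan states no figure to reproduce here. The check is whether each PRI time named as an endpoint appears among the times at which PRI blood is to be drawn.

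**Inputs**

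- Primary time: 2 h after the loading dose (Abstract; Study Objectives).
- Secondary times: 0.5, 1, 8 and 24 h (Study Objectives).
- Listed PRI draws: predose, 0.5, 1, 8 and 24 h (paragraph after Figure 1).

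**Comparison**

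| PRI time | Role | In the sampling list? |
|---|---|---|
| predose | baseline covariate | yes |
| 0.5 h | secondary | yes |
| 1 h | secondary | yes |
| 2 h | primary | **no** |
| 8 h | secondary | yes |
| 24 h | secondary | yes |

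The list has 5 draws. It covers 4 of 4 secondary times and 0 of 1 primary times. No PRI sample falls between 1 h and 8 h, a gap of 8 − 1 = 7 hours that contains the primary time.

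**Could another scheduled sample serve?** The only other bloods in the paragraph are CK-MB, troponin I, myoglobin and C-reactive protein. None is a PRI measurement. Their pre-PCI draw is also not fixed at 2 h, because PCI may take place anywhere from 2 to 72 h after the loading dose.

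**Could the analysis supply the value?** Statistical and Analytical Plans proposes a mixed-effects model for the pharmacodynamic assessments. If no participant has a 2-hour observation, such a model can give a 2-hour treatment contrast only by assuming a shape for the time course between 1 h and 8 h. The article states no such shape. The result would also be a modelled quantity, whereas the endpoint is defined as a measured PRI.

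**After correction.** The set predose, 0.5, 1, 2, 8 and 24 h has 6 draws and covers the primary time and all four secondary times.

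**The case against.** The strongest reply is that the intent is not in doubt. The 2-hour time is stated twice, in the same terms, and Study Objectives belongs to the same Methods section as the sampling sentence. A reader who takes the two together would draw at 2 hours. Study Design and Study Drug Administration also refers to Figure 1 for the study flow. That figure is not shown in the available text and may list the draw. The article is a condensed account, and the full protocol may have the schedule right. Nothing in the article says that the eight centres work from this sentence.

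Most of this stands, and it limits what can be claimed. A reader might infer that the trial had no plan to measure its primary outcome, or that some share of primary data would be lost. The documents support neither. They do not show what the sites were given, and they offer no basis for a figure on lost information.

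The reply does not remove the contradiction. Condensation explains details left out; it does not explain a definite list that names every PRI time except the primary one. Clear intent elsewhere makes the correction easy, but the sentence is still wrong as written.

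**Conclusion.** The point holds as an internal inconsistency. The PRI sampling list disagrees with the Abstract and Study Objectives on the one time that matters most. Read literally, it provides five PRI samples and none for the primary endpoint. The likeliest cause is a drafting omission.

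Confidence in the inconsistency is high, because it rests on plain statements in the text. Confidence that any sample was actually missed is not warranted: that would require the site-facing schedule to carry the same omission, which cannot be seen. The omission is not evidence of a deliberate design choice. It needs correcting because it concerns measurement of the primary endpoint, even though the probable cause is trivial.

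**What to change.** Reconcile the sampling sentence after Figure 1 with the Abstract and Study Objectives by adding 2 hours to the PRI list, so that it reads predose and 0.5, 1, 2, 8 and 24 hours after the loading dose. Then confirm that Figure 1, the full protocol and whatever schedule the sites use give the same times.

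The cost is one inserted time point and a consistency check. Set against the list as written, it is one more draw per participant (6 instead of 5), but the primary endpoint already requires that draw. No endpoint, sample-size figure or analysis changes.
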